**Figure 1. f1:**
[figure not shown]
Flow chart showing study methodology.

We selected a 15% reduction in both alkaline phosphatase (ALP) and gamma-glutamyl transferase (GGT) as our primary biochemical endpoint based on evidence from previous trials in cholestatic liver disease. Specifically, the landmark study by Nevens et al., published in The New England Journal of Medicine (2016), evaluated obeticholic acid in patients with primary biliary cholangitis and used a composite endpoint that included a ≥15% reduction in ALP as part of the therapeutic response criteria.

Although this trial was not conducted in post–liver transplant patients, it provided a strong precedent for using ALP-based endpoints to assess treatment response in cholestatic conditions. We extended this rationale by including GGT alongside ALP, as the combination of these two enzymes provides a more comprehensive and sensitive assessment of cholestasis, particularly in the post-transplant setting where bile duct injury and graft function are dynamic.

Given the lack of clinical trials of OCA in the liver transplant population, this combined biochemical endpoint serves as a reasonable and evidence-informed surrogate marker of response in our study.

Secondary endpoint serum markers are being assessed using an enzyme-linked immunosorbent assay (ELISA) [ELK Biotechnology™] at the centralized biochemistry laboratory. Blood samples collected during the one-month and twelfth-month post-transplant follow-up visits are being used for ELISA testing.

In addition, demographics, patient characteristics, and other critical study details (e.g., medication history, medical history, social habits, family history, and use of other medical systems) are being collected through direct patient or bystander interviews, doctor consultation notes, hospital health information systems, and case records. The collected data is being transcribed into a pre-designed proforma (data collection form) by the investigator.

### Biopsy and rejection evaluation

A biopsy is being performed when suspected rejection (unexplained rise in transaminases) is observed. The biopsy results are being evaluated based on the Rejection Activity Index score and the Banff criteria. Data on the frequency and duration of the first biopsy-proven acute rejection (BPAR) episode (within six months of transplantation) that requires therapy are being recorded. Any biliary system-related strictures, leaks, or anastomosis issues are being documented. Early allograft dysfunction (EAD) is being assessed using the criteria developed by Olthoff et al.
^
7,
32
^

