### Secondary outcomes

•Assessment of biochemical markers (Liver function tests, metabolic profile, CRP, tacrolimus levels).•Molecular markers (fibroblast growth factor 19 (FGF-19), transforming growth factor β (TGF-β) level, Cytokeratin 18 level, Serum autotaxin level, Bile Salt Export Pump levels (BSEP), Plasma bile acid levels.•Biopsy-proven acute or chronic rejection.•Incidence of biliary complications.•All-cause mortality.•Any adverse events.•Death due to acute or chronic rejection.•Quality of life.

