**Blinding**

This is an open-label study. Blinding is not feasible due to the nature of the interventions. Given the difference in tablet size and dosing frequency (three times daily for UDCA vs once daily for OCA), blinding is not being done.

Primary outcomes will be based on objective biochemical parameters to minimize bias.

Given the difference in tablet size and dosing frequency (three times daily for UDCA vs once daily for OCA), blinding is not being done.

Follow-up visits for physical examinations and safety assessments are being scheduled during the study period at the following intervals: one month, three months, six months, and twelve months post-transplant (
Figure 1).

Study assessments were initiated at one month post-transplant because a substantial proportion of our liver transplant recipients are high-MELD patients who often have markedly elevated bilirubin and cholestatic enzyme levels in the immediate postoperative period. In addition, transient elevations in liver function tests are commonly observed during the early post-transplant phase due to ischemia–reperfusion injury, surgical factors, sepsis, or early graft dysfunction or rejection.

In live donor liver transplantation, particularly among high-MELD recipients, these fluctuations are often pronounced during the first few weeks after surgery. Therefore, a four-week stabilization period was allowed to enable resolution of early postoperative variability and to ensure that subsequent biochemical measurements more accurately reflect the effects of the study intervention rather than perioperative factors.

Liver function tests, C-reactive protein (CRP), platelet count, prothrombin time/international normalized ratio (PT/INR), fasting blood sugar (FBS), tacrolimus concentration, and other relevant parameters are being measured at each follow-up visit. Lipid profile—including total cholesterol, low-density lipoprotein (LDL), high-density lipoprotein (HDL), very low-density lipoprotein (VLDL), and triglycerides (TG)—as well as glycosylated hemoglobin (HbA1c) levels, are being assessed at pre-transplant admission, and at three, six, and twelve months post-transplant.

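### The listed secondary outcome is any biopsy-proven acute or chronic rejection, but the only stated recording rule covers the first treated acute episode within six months

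*Protocol article*

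**What the plan says.** All references are to the protocol article.

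- **Secondary outcomes** lists "Biopsy-proven acute or chronic rejection" and, separately, "Death due to acute or chronic rejection". Neither entry has a time point. The rejection entry has no treatment condition and no limit to a first episode.
- **Biopsy and rejection evaluation** opens with the procedure: "A biopsy is being performed when suspected rejection (unexplained rise in transaminases) is observed". Grading follows: "The biopsy results are being evaluated based on the Rejection Activity Index score and the Banff criteria". Neither sentence is limited by time, type of rejection or treatment.
- The same section then gives the only rule for recording rejection data. It begins "Data on the frequency and duration of the first biopsy-proven acute rejection (BPAR" and continues "episode (within six months of transplantation) that requires therapy are being recorded".
- **Blinding** states that the trial is open-label and sets follow-up visits at "one month, three months, six months, and twelve months post-transplant". Its stated protection against bias, objective biochemistry, is claimed for the primary outcomes.
- **Rationale** names the effect of obeticholic acid on rejection as something the study will examine.

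**The concern.** The outcome list and the recording rule describe different events. A team that follows the recording rule literally would collect a subset of what the outcome list promises. Two things are at stake.

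**Completeness.** Chronic rejection is half of the named outcome and has no stated capture rule. The same is true of acute rejection first seen in months 6 to 12, of repeat episodes, and of biopsy-proven episodes that were not treated.

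**Bias.** The condition that an episode must require therapy puts a clinical decision between the biopsy result and the event count. In an open-label trial that decision can be made with knowledge of the arm. If the threshold for treating differs between arms, the counts differ even when the histology does not. Two definitions in one document also leave room to choose between them after open data have been seen.

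**Working it through.** The documents give no rejection rate and no planned effect on rejection, so there is no figure to reproduce. The check is a comparison of the texts.

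| Feature | Secondary outcomes | Biopsy procedure and grading | Recording rule |
|---|---|---|---|
| Type | Acute or chronic | Any suspected rejection | Acute |
| Order | Not limited | Not limited | First episode |
| Window | None stated | None stated | Six months from transplantation |
| Treatment | No condition | No condition | Must require therapy |

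1. The rule is narrower than the outcome on all four features.
2. Visits continue to month 12 and the rule stops at month 6. As written it spans 6 of 12 months, or half of scheduled follow-up.
3. The rule is unclear in itself. It asks for the frequency of a first episode, which a patient can have at most once. It may mean the proportion of patients with such an episode, or the number of episodes, and the second would contradict the restriction to the first.
4. The next sentence of the section, on biliary strictures, leaks and anastomotic problems, asks for all such events without restriction. This makes it natural to read the limits on rejection as deliberate.

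**Illustration only; every rate and share here is an assumption.**

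*Late first episodes.* Take 115 per arm, the middle of the planned 110 to 120, and a 12-month risk of 20%: 115 × 0.20 = 23 patients. If 10% to 40% of first episodes fall after month 6, then 23 × 0.10 = 2.3 and 23 × 0.40 = 9.2, or about 2 to 9 per arm outside the window. Chronic and untreated episodes would add to this.

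*Power.* Take n = 108 per arm, two-sided 0.05, and a capture share f equal in both arms, so that each risk becomes f × p. With p̄ the mean of the two captured risks, power = Φ{[|p1 − p2| − 1.96·√(2p̄(1 − p̄)/n)] / √([p1(1 − p1) + p2(1 − p2)]/n)}.

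| Assumed true risks | f = 1 | f = 0.8 | f = 0.6 |
|---|---|---|---|
| 30% vs 15% | 75.5% | 63.3% | 49.0% |
| 20% vs 10% | 53.9% | 44.0% | 33.7% |

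For example, with 30% vs 15% and f = 0.8 the captured risks are 24% and 12%, p̄ = 0.18, and power = Φ[(0.12 − 1.96 × 0.0523)/0.0516] = Φ(0.34) = 63.3%. This shows the direction of the effect. It is not an estimate for this trial, whose sample size rests on alkaline phosphatase and not on rejection.

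**The case against.** The strongest reply is that the recording sentence does not claim to be exhaustive. It does not say that only these episodes are recorded. The two sentences before it have biopsies done and graded without limit of time, type or treatment, so the third may merely ask for extra detail on early treated acute episodes. Study data are taken from consultation notes, hospital information systems and case records into a pre-designed form. The article lists that form among its deposited files, but it is not shown here, and a field for late or chronic rejection may exist on it. Rejection is also one of several secondary outcomes for which the trial was not sized.

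Much of this stands, and it rules out stronger readings that a reader might infer:

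- **That rejection is a 12-month outcome by the protocol's own text.** The outcome list gives no time point. Twelve months comes from the visit schedule.
- **That late, chronic and untreated rejections are dropped, or that the outcome cannot be reported.** No sentence says they go unrecorded, and biopsy reports in hospital records should be retrievable.
- **That a known number of events is lost.** Any count rests wholly on assumed rates.

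The reply does not remove the mismatch. A condensed article may leave field-level detail to another document, but here it states a specific rule that differs from its own outcome list. The reader cannot tell which of the two defines the endpoint.

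**Conclusion.** The point holds as an inconsistency between two stated texts. The listed outcome is acute or chronic biopsy-proven rejection without limits. The only stated recording rule covers the first acute episode, within six months, that requires therapy. If that rule defines the endpoint data, it does not yield the listed outcome, and it makes an event depend on an unblinded treatment decision.

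The size is unknown because no rejection rate is given. What can be stated is scope: the rule covers one of two named types, 6 of 12 months of scheduled follow-up, and first treated episodes alone. The primary endpoint is not affected. The text should be corrected because rejection is a declared aim and the correction is cheap.

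**What to change.** Give the rejection outcome one definition and one window, and use the same words in both sections.

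- **Preferred.** Record every biopsy-proven acute or chronic rejection from randomisation to month 12, with date, Banff grade, Rejection Activity Index and whether it was treated. Keep first treated acute rejection within six months as a supportive outcome, and say whether its frequency means patients or episodes.
- **Alternative.** Restrict the listed secondary outcome openly to first treated acute rejection within six months, and drop the claim to compare chronic rejection.

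Either option reconciles the text. The first keeps the stated aim and removes the treatment condition from the main count. A time-to-event analysis with death as a competing event is an option, but the inconsistency does not require it.

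The cost is one addition to the case report form, if the field is not already there, and retrieval of biopsy reports for patients already enrolled. Recruitment is still open. Only data recording changes, not patient care.

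The change does not make ascertainment blind. Biopsies are taken for cause, and staff who know the arm can still influence who is biopsied. The report should state this as a limitation.

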### Adverse reactions and causality assessment

Adverse events are being captured by direct interview of patients during the routine follow-up visits. We are capturing the pruritus by physical examination, vital signs and 5D pruritus questionnaire and documented systematically using structured Case Report Forms (CRFs) to ensure standardized data collection and analysis. The Naranjo algorithm will be used to establish causality and then classify them as definite, probable, possible, or unlikely.

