### Eligibility & exclusion criteria

All adult patients undergoing live donor liver transplantation during the study period are being included. Recipients who are less than 18 years of age, those undergoing deceased donor liver transplants, ABO-incompatible transplants, retransplant cases, those not surviving beyond 30 days, and patients lost to follow-up during the study period, are being excluded. We excluded patients who were randomized into the trial but died within the first 30 days. This decision was based on the fact that early mortality in this period is most commonly attributable to sepsis or technical complications. Including such patients would not be appropriate for evaluating interventions aimed at the management of cholestasis, which usually occur 2 to 3 weeks after surgery. Mortality within 30 days, purely secondary to the adverse effect of the drug, with no other technical (vasculo-biliary), septic or immunological cause is extremely unlikely. Obeticholic acid was administered at a low dose of 5 mg once daily, which represents the standard starting dose used in clinical trials. Published studies have demonstrated acceptable tolerability at this dose, with pruritus being the most commonly reported adverse event and no evidence of treatment-related early mortality.

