**Allocation**

Participants are randomized in a 1:1 ratio using a computer-generated permuted block sequence. Allocation concealment will be ensured using sequentially numbered, sealed opaque envelopes opened by the study pharmacist on postoperative day two.

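### General adverse events are collected by patient interview from month 1, although allocation is on day two; early events rest on recall, and patients who die or are lost before a visit have no named source

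*Protocol article*

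**What the plan says.** Under Adverse reactions and causality assessment, the protocol article states: "Adverse events are being captured by direct interview of patients during the routine follow-up visits". The follow-up schedule appears under Blinding, with visits at "one month, three months, six months, and twelve months post-transplant". The same section adds: "Study assessments were initiated at one month post-transplant".

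Under Allocation, treatment is assigned from "sealed opaque envelopes opened by the study pharmacist on postoperative day two". The day of first dose is not given. The section Eligibility & exclusion criteria, however, argues about "Mortality within 30 days, purely secondary to the adverse effect of the drug", which makes sense only if study drug is given before day 30. That section also says: "We excluded patients who were randomized into the trial but died within the first 30 days". Patients lost to follow-up are excluded too.

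"Any adverse events" is listed under Secondary outcomes, with no start date or collection window.

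Other routes exist for particular events. On itching the article says: "We are capturing the pruritus by physical examination, vital signs and 5D pruritus questionnaire". Biopsy and rejection evaluation covers biliary problems and biopsy-proven rejection. Safety monitoring mentions scheduled clinical and laboratory checks. All-cause mortality and death from rejection are secondary outcomes in their own right.

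**The concern.** An interview needs a patient who is alive and comes back. Where that is the stated source for general adverse events, the completeness of the safety data depends on survival and retention, both of which may differ between arms. The patients with the worst courses are the likeliest to have no interview covering their last weeks.

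The first weeks matter most. The article defends excluding deaths within 30 days by arguing that a death caused purely by the drug in that period is very unlikely. The stated method collects general adverse events from that period only afterwards, from those who survived it, so the trial's own data could hardly test the argument. The four-week stabilization period is justified for biochemical measurements; nothing in that reasoning supports delaying safety capture.

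The trial is open-label, and its stated safeguard against bias, objective laboratory values, is claimed for the primary outcomes. Recalled symptoms do not have that protection. The article also acknowledges that clinical trials of obeticholic acid in transplant recipients are lacking, so the safety comparison is among the more informative things this trial can offer.

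**Working it through.** The article gives no figure for this point, so there is nothing to reproduce. The check sets the sections side by side and adds two small calculations.

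**Step 1. Timeline**

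| Time | What happens | Section |
|---|---|---|
| Day 2 | Allocation opened | Allocation |
| Before day 30 | Dosing implied, first-dose day not stated | Eligibility & exclusion criteria |
| Up to day 30 | Randomized patients who die are excluded | Eligibility & exclusion criteria |
| Month 1 | First follow-up visit, first interview | Blinding |
| Months 3, 6, 12 | Later visits | Blinding |

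The gaps between visits are 3 − 1 = 2 months, 6 − 3 = 3 months and 12 − 6 = 6 months.

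**Step 2. Length of the first window.** Take month 1 as day 28 to 30 and the year as 365 days. The window from allocation is 28 − 2 = 26 to 30 − 2 = 28 days. As a share of the post-allocation year this is 26/363 = 7.2% to 28/363 = 7.7%. If dosing starts later than day two, the exposed part of the window is shorter.

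**Step 3. Who has a source for general non-fatal adverse events, by the stated method?**

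- *Alive at month 1:* yes, but events from the preceding weeks are collected by recall.
- *Dies by day 30:* none named, and the patient is excluded.
- *Dies after day 30, between visits:* interviews up to the last visit; nothing named for the interval after it.
- *Lost to follow-up:* as above for data, and the patient is also excluded.

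**Step 4. What does not depend on the interview?** Pruritus is also assessed by examination and questionnaire. Biliary problems are documented, and rejection is identified by biopsy prompted by an event. Laboratory values are measured, and deaths are an outcome. The weakness is therefore confined to the other adverse events.

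**Step 5. How many patients might have no interview at all?** The article gives no 30-day mortality. As an assumption only, 3% to 15% of 216 randomized patients gives 216 × 0.03 = 6.5 to 216 × 0.15 = 32.4, or about 6 to 32 patients in both arms together. This counts patients who die before a first interview. It does not count lost events.

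**The case against.** The strongest reply is that this is a condensed article. Sources and reporting periods for adverse events normally sit in the full protocol and the case report form. A data collection form is listed under Data Availability but is not shown, so record-based capture may already be in place. The text following Figure 1 names bystander interviews, consultation notes, hospital information systems and case records as sources for patient characteristics and other study details, with examples that are not exhaustive. Use of records for adverse events is thus not ruled out.

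Part of this stands. It limits how firmly one can say what happens in practice. It does not remove the point, because the article does more than stay silent: it states a method for adverse events, and that method is narrower than the sources it lists for other data. If practice is broader, the statement should be corrected.

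Three stronger readings are tempting, and the article does not support them:

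- A reader might infer that the interview is the only safety source. The text does not say so, and the routes in Step 4 contradict it.
- A reader might infer that every event between day two and month 1 is missed. Nothing confines the month-1 interview to events after month 1; for survivors the problem is delay and recall, not certain loss.
- A reader might apply the Introduction's 85% first-year success figure to 110 to 120 patients per arm and conclude that 110 × 0.15 = 16.5 to 120 × 0.15 = 18 per arm lose their adverse event data. That figure is general background for liver transplantation. It would also cover early deaths, whom this trial excludes. Missing the month-12 interview is not the same as losing adverse events: a patient who dies at month 8 could have been interviewed at months 1, 3 and 6.

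The exclusion of deaths within 30 days is also a fault of the analysis population in its own right. It matters here because it removes the same patients whom the interview cannot reach.

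**Conclusion.** The point holds in limited form. The stated method ties general adverse events to interviews that begin 26 to 28 days after allocation. Early events in survivors then rest on unblinded recall, and no source is named for general non-fatal events in patients who die or are lost before a visit.

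The number of events affected, and any imbalance between arms, cannot be calculated from the article; the range in Step 5 rests wholly on an assumed mortality. The conclusion assumes that the published sentence describes the method as applied and that dosing begins before month 1, as the eligibility text implies. It is an improvement that should be made, affecting the safety comparison and not the primary biochemical endpoint.

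**What to change.** Amend Adverse reactions and causality assessment so that adverse and serious adverse events are recorded from first study dose to month 12 for every patient who receives study drug. Name ward notes, laboratory results and readmission records as sources, drawn from the hospital systems the investigators already use, and keep the visit interview as an addition. State the day of first dose as it is actually applied, so that the start of the safety period is defined.

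Tabulate safety by arm from first dose. Include patients who die within 30 days and those later lost, and show the period before the month-1 visit separately.

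The cost is some extra chart abstraction and one more safety table. Recruitment is still under way, and the charts of patients already enrolled can be read retrospectively. If the full protocol or case report form already provides for this, correcting the published sentence and adding the table would be enough.
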